# The BE GONE trial study protocol: a randomized crossover dietary intervention of dry beans targeting the gut microbiome of overweight and obese patients with a history of colorectal polyps or cancer

**DOI:** 10.1186/s12885-019-6400-z

**Published:** 2019-12-18

**Keywords:** Colorectal cancer survivors, Precancerous colorectal polyps, Dry beans, Obesity, Diet, Gut microbiome, Metabolome

## Abstract

**Background:**

Mouse and human studies support the promise of dry beans to improve metabolic health and to lower cancer risk. In overweight/obese patients with a history of colorectal polyps or cancer, the Beans to Enrich the Gut microbiome vs. Obesity’s Negative Effects (BE GONE) trial will test whether and how an increase in the consumption of pre-cooked, canned dry beans within the context of usual diet and lifestyle can enhance the gut landscape to improve metabolic health and reduce cancer risk.

**Methods/design:**

This randomized crossover trial is designed to characterize changes in (1) host markers spanning lipid metabolism, inflammation, and obesity-related cancer risk; (2) compositional and functional profiles of the fecal microbiome; and (3) host and microbial metabolites. With each subject serving as their own control, the trial will compare the participant’s usual diet with (intervention) and without (control) dry beans. Canned, pre-cooked dry beans are provided to participants and the usual diet continually assessed and monitored. Following a 4-week run-in and equilibration period, each participant provides a total of 5 fasting blood and 6 stool samples over a total period of 16 weeks. The intervention consists of a 2-week ramp-up of dry bean intake to 1 cup/d, which is then continued for an additional 6 weeks. Intra- and inter-individual outcomes are assessed across each crossover period with consideration of the joint or modifying effects of the usual diet and baseline microbiome.

**Discussion:**

The BE GONE trial is evaluating a scalable dietary prevention strategy targeting the gut microbiome of high-risk patients to mitigate the metabolic and inflammatory effects of adiposity that influence colorectal cancer risk, recurrence, and survival. The overarching scientific goal is to further elucidate interactions between diet, the gut microbiome, and host metabolism. Improved understanding of the diet-microbiota interplay and effective means to target these relationships will be key to the future of clinical and public health approaches to cancer and other major diet- and obesity-related diseases.

**Trial registration:**

This protocol is registered with the U.S. National Institutes of Health trial registry, ClinicalTrials.gov, under the identifier NCT02843425. First posted July 25, 2016; last verified January 25, 2019.

## Background

A growing body of research indicates that diet can change the vast community of bacteria (or microbiome) known to affect obesity and cancer risk [1–6]; and presents a potentially effective strategy to improve outcomes among high-risk patients [7]. Provocative findings from controlled human feeding studies reveal that diet-induced changes in the gut microbiome can be both rapid and profound, but easily reversed [8, 9] signifying that beneficial bacteria or microbial communities may need to be continually cultivated to ultimately improve chronic health problems and to prevent latent cancers or their recurrence. Simple strategies are needed for overweight and obese patients who have likely suffered from a history of challenges surrounding food and weight control, as well as for high-risk individuals who prefer dietary approaches to drugs or who cannot tolerate other therapies.

Dry beans (*Phaseolus vulgaris*) are a prebiotic food source rich in bioactive compounds with anti-inflammatory, anti-lipidemic, and chemopreventive properties [10–12]. Despite supportive evidence from parallel obese mouse and human studies [13–17] dry beans are not a particularly popular or well-recognized dietary strategy for reducing the recurrence of colorectal polyps or cancer. One potential barrier to clinical and public health implementation is that none of the previous studies address whether simply increasing or adding beans to the usual diet, as suggested by observational findings in the Polyp Prevention Trial [18], is sufficient to improve gut and overall metabolic health to lower cancer risk. Secondly, the gut microbiome, a potentially transformative tool, has not yet been assessed in a whole dry bean intervention among high-risk, overweight or obese patients with a history of colorectal polyps or cancer.

The BE GONE trial is designed test whether and how a relatively simple increase in canned, pre-cooked dry bean intake can enrich the gut microbiome of overweight/obese patients with a history of precancerous colorectal polyps or colorectal cancer. The trial is also designed to assess whether changes in the gut microbiome precede or parallel changes in other established markers of gut health, metabolic health, and obesity-related cancer risk.

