#### Randomization and follow-up visits (V0-V4)

Participants who complete the run-in are randomized to begin the intervention diet or to continue the control diet for an additional 8 weeks (Fig. 2). The randomization list was generated by an independent analyst and allocated by a research team member not directly interacting with participants. Participants are block-randomized according to no use vs. regular use of chronic disease medications (namely statins and metformin) commonly prescribed to our target population of overweight/obese high risk CR patients. The randomization visit (V0) and all subsequent trial visits require a fasting blood draw and are conducted in the morning. There are a total of 5 in-person visits every 4 weeks from the randomization visit. At each visit, anthropometry and blood pressure are measured. Medications and changes in health status are reviewed. In addition, a stool sample is brought to each visit (Fig. 3).

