#### Ramp-up and dose

Participants are provided with a supply of pre-cooked, canned organic navy beans (*Phaseolus vulgaris*) [19–21] stored in water with sea salt. To examine dose-response and temporal effects and to avoid gastrointestinal (GI) discomfort, participants are counseled to incorporate the canned beans in to their usual diet in a stepwise fashion during the intervention sequence (Fig. 3). Participants begin by consuming ½ cup (1 serving) of beans over the 2 week ramp-up period. At the end of the ramp-up period, participants provide a stool sample by mail. Following the ramp-up, participants consume 1 cup (2 servings) per day for an additional 6 weeks. At week 8, participants who complete the intervention diet crossover to the control diet and vice versa. Two ½ cup servings (260 g) of canned navy beans provide 220 kcal, 14 g protein, 38 g carbohydrate (~ 12% of 2000 kcal diet), 16 g of fiber (~ 64%), 200 mg of sodium (~ 8%), 660 mg of potassium (~ 22%), 12% of daily value for calcium and 20% of daily value for iron.

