#### Data analysis

Change scores of outcomes will be based on the differences between the beginning and the end of each study period (Figs. 2 and 3); and by subtracting the change experienced over the control period from the change experienced over the intervention period. Paired t-tests will be conducted to assess whether there are significant differences between changes in each subject’s baseline and follow-up outcomes over the equilibration, control, and intervention period. Two-way ANOVA will be used to test for differences in the change scores by categories of other variables. Generalized linear mixed models (GLMMS) will be used to explore potential order or carry-over effects, and to adjust for other potential confounders and assess potential effect modifiers measured at pre-study and study visits. Hierarchically clustered phylotypes will be constructed by the similarity of their dynamics [31] across study periods and subjects and in relation to other variables, such as usual diet pattern.

To examine the effect of a dry bean intervention on the diversity and composition of the gut microbiome, the primary outcome measure will be changes in stool *16S* rRNA gene profiles at baseline and follow-up for each cross-over period. We will quantify the microbial diversity within each subject at each time point; and calculate change scores and construct GLMMs (see above) with repeated measurements (PROC MIXED). We will also construct hierarchically clustered phylotypes by the similarity of their dynamics [31] across study periods and subjects and in relation to other variables, such as usual diet pattern.

To examine the relationship between changes in the gut microbiome and changes in fecal and serum markers, we will follow the procedures described above to quantify changes; and to assess the effects of other variables on these changes. We will assess Spearman correlations of changes in the gut microbiome with changes in fecal and serum markers and employ computational methods to identify taxa associated with differences in serum and fecal markers [49].

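### The described correlations of whole-period changes cannot show whether the microbiome moves first, and the common fixed escalation cannot separate dose from duration of exposure

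*Protocol article*

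**What the plan says.** **Aim.** The Background states that the trial is designed to "assess whether changes in the gut microbiome precede or parallel changes in other established markers".

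**Analysis.** The Data analysis section defines change scores from the start to the end of each study period, then subtracts the control-period change from the intervention-period change. For the link between microbiome and markers it carries those procedures over and adds: "We will assess Spearman correlations of changes in the gut microbiome with changes in fecal and serum markers". It names no lag or ordering in time.

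**Dose.** The Ramp-up and dose section gives the purpose of the stepwise intake: "To examine dose-response and temporal effects and to avoid gastrointestinal (GI) discomfort". The sequence is the same for everyone: "Participants begin by consuming ½ cup (1 serving) of beans over the 2 week ramp-up period", then "Following the ramp-up, participants consume 1 cup (2 servings) per day for an additional 6 weeks".

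**Samples.** "At the end of the ramp-up period, participants provide a stool sample by mail". The section on randomization and follow-up visits says "There are a total of 5 in-person visits every 4 weeks from the randomization visit", each with fasting blood and a stool sample. The abstract gives the total after run-in: "each participant provides a total of 5 fasting blood and 6 stool samples over a total period of 16 weeks". The Outcome measures section places paired stool and blood at baseline, week 4 and week 8 of each period.

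**The concern.** The article makes two claims about what the trial can examine, and each has to be supported by the analysis or the design.

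- **Precedence.** A correlation between two changes over the same interval is symmetric. It holds no information on which change came first.
- **Dose-response.** If all participants pass through the same amounts in the same order, a difference between the lower and the higher step may reflect the amount, the time on beans, or both.

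At stake is interpretation. Stool is first taken two weeks into the bean period and blood not until week 4, so the microbiome could appear to change first merely because it was sampled first. A response that grows with time on beans could likewise be reported as a response to dose.

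**Working it through.** **1. Sample count.** Five visits four weeks apart fall at weeks 0, 4, 8, 12 and 16, giving 5 blood and 5 stool samples. The abstract gives 5 blood and 6 stool, so 6 − 5 = 1 stool is left, which is the ramp-up sample. The count reproduces. At the lower step there is therefore one stool, no blood and, by this count, no control-period week-2 stool. The pre-visit stool comes before the run-in and is outside the count.

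**2. Does the whole-period correlation depend on order?** Illustrative model, all inputs assumed: each participant has a response of variance 1, and each measurement has independent error with SD 0.75. The share of the response reached at weeks 0, 4 and 8 is 0, 1, 1 (early), 0, 0.6, 1 (intermediate) or 0, 0.2, 1 (late). If the microbiome changes by share *a* over one interval and the marker by share *b* over the same or another non-overlapping interval, then

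correlation = a·b / √[(a² + 2·0.75²)(b² + 2·0.75²)], with 2·0.75² = 1.125.

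- Whole period: a = b = 1 in every scenario, so the correlation is 1/2.125 = 0.47 whichever moves first.
- Microbiome leads, microbiome weeks 0–4 with marker weeks 4–8: 0.8/√(2.125 × 1.765) = 0.41. Reverse lag: a = 0, so 0.
- Parallel, either lag: 0.6 × 0.4/√(1.485 × 1.285) = 0.17.

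Mean Spearman correlations simulated at n = 60 from the same model agree:

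| Scenario | Weeks 0–8, both | Microbiome 0–4, marker 4–8 | Marker 0–4, microbiome 4–8 |
|---|---|---|---|
| Microbiome leads | 0.44 | 0.39 | 0.00 |
| Parallel | 0.45 | 0.16 | 0.17 |
| Marker leads | 0.45 | 0.00 | 0.39 |

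The described analysis gives the same answer in all three rows. The two lags, computed from visits already planned, tell the rows apart on average.

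**3. How precise would the lagged contrast be?** Expressed as bean minus control, the error variance doubles to 4·0.75² = 2.25. This assumes independent errors and no individual drift on control; the two periods in fact share the crossover visit, which is ignored here. When the microbiome leads, the forward lag becomes 0.8/√(3.25 × 2.89) = 0.26, against 0 in reverse. On the Fisher z scale the standard error of one correlation is about 1/√(60 − 3) = 0.13. The difference of two, treated as independent, has about 0.13 × √2 = 0.19. With atanh(0.26) = 0.27, the difference is about 0.27/0.19 = 1.4 standard errors with all 60 participants complete. That is exploratory precision.

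**4. Can dose be separated from time?** Take the stool schedule: control weeks 0, 4, 8; bean weeks 0, 2, 4, 8, with prescribed amounts 0, 0.5, 1, 1 cup (reading the ramp-up step as a daily amount). A model with an intercept, week effects (4, 8) and bean-by-week effects (2, 4, 8) has rank 6. The dose column equals 0.5·(bean, week 2) + 1·(bean, week 4) + 1·(bean, week 8), so adding it leaves the rank at 6. With free week effects no information on dose remains.

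Within the bean period the correlation of dose with week is 4.25/√(35 × 0.6875) = 0.87. It is below 1 because weeks 4 and 8 share one prescribed amount. For blood the prescribed amounts observed are only 0 and 1 cup.

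**The case against.** A reader might infer that the trial can show neither order nor dose-response at all. The documents do not support that, for these reasons.

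- **The design can address order, coarsely.** Paired samples exist at weeks 0, 4 and 8 of both periods. The limit lies in the analysis described.
- **The aim has two branches.** The planned correlations do address parallel change, which is also how the Outcome measures section words the primary outcome.
- **Repeated-measures mixed models are named**, as is clustering of phylotypes by their dynamics. This stands in part. The mixed model with repeated measurements is stated for diversity. A model of one variable over time does not test whether it leads another, and the clustering is not set up as a test of order against the markers.
- **The week-2 stool is not worthless.** Fecal markers could be assayed in it, so the missing pairing concerns blood. Nor does mailing set it apart: the sample collection section allows express mail return for stool generally.
- **Dose and time are not perfectly aligned**, as the 0.87 shows, and the control period removes general time trends at weeks 4 and 8. What stays entangled is dose with duration of exposure. Separating them needs an assumed time shape. The reduced intake allowed for tolerance adds variation in dose, but it is self-selected.
- **Dose-response appears once**, as part of the rationale for the ramp-up. No stated objective, power figure or test depends on it.

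It can also be said that an article leaves lag structure to a fuller plan. That would answer a complaint of missing detail. Here, however, the article states a method for the microbiome–marker link, and that method cannot answer the precedence half of the stated aim. No analysis plan can supply a dose contrast that the schedule does not contain.

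**Conclusion.** The concern holds in this limited form. Start-to-end change correlations cannot distinguish a leading from a following microbiome (0.44, 0.45 and 0.45 in the illustration), while the planned week 0, 4 and 8 samples could do so coarsely. The size of the lagged correlations rests on the assumed response curves and error SD. The symmetry of the whole-period correlation does not.

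The dose-response purpose is not supported by the design: with free week effects, dose adds nothing to the rank (6 before and after), and there is no blood at the lower step. The absence of a control-period week-2 stool is inferred from the sample count.

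The consequence is for interpretation of exploratory results. No primary inference, sample size or decision rule depends on either claim. The article's power figure for correlated changes concerns a single correlation, so it does not describe the precision of a difference between lags and is not used here.

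**What to change.** 1. Add an exploratory cross-lagged analysis, expressed as bean minus control: microbiome change over weeks 0–4 with marker change over weeks 4–8, set against marker change over weeks 0–4 with microbiome change over weeks 4–8. Base any statement that the microbiome precedes the markers on the difference between the two lags, with a confidence interval. Keep the whole-period correlations for parallel change.
2. State the limits: precision is low at n = 60, and changes in blood markers within the first four weeks cannot be ordered against the microbiome.
3. Report the week-2 stool result as descriptive.
4. Describe the ramp-up analysis as a time course under a fixed escalation in place of dose-response.

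This needs analysis text and wording only, with no new samples and no change to the intervention. The cost is that the dose-response claim is given up and that the lagged contrast may well be inconclusive.

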### Hypotheses and objectives

Given the prebiotic and antineoplastic properties of beans, and that changes in host diet rapidly alter the composition of gut microbiota, we expect that the dry bean intervention among overweight/obese individuals positive for precancerous colorectal (CR) polyps or CR cancer (herein referred to as “high-risk CR patients”) will enrich or balance the gut microbiome with beneficial bacteria. We further hypothesize that these changes will correlate with improvements in microbial metabolites and host biomarkers that modulate host inflammation and metabolism; and/or lower levels of metabolites positively correlated with obesity-related factors. Characterizing fecal microbiota, blood markers, and metabolites to elucidate interactions between diet, the gut microbiome, and host metabolism will provide insight into overlapping obesity and cancer pathways and more effective methods of upstream dietary prevention (Fig. 1).

**Fig. 1 Fig1:**
[figure not shown]
Fiber-rich diet shapes the composition, function and metabolic output of the gut microbiome. Diet modulates host metabolism and inflammation both directly and through the activities of the gut microbiome

### Primary objective

To examine the effect of increased consumption of dry beans on the gut microbiome and blood biomarkers in high-risk CR patients otherwise consuming their usual diet.

### Secondary objective

To develop the field and research procedures of a prospective randomized crossover dietary intervention of whole dry beans, including compliance in our target patient population and the modifying effects of the baseline gut microbiome and usual diet on participant’s response to the intervention.

### Outcome measures

The primary outcome measures are parallel changes in gut microbiota profiles and circulating lipid and adipocytokine profiles from serial stool and fasting blood samples collected at baseline, week 4, and week 8 for each cross-over period. Secondary outcomes include fecal surrogates of gut inflammation and host and microbial metabolites.

## Methods/design

### Overview of trial design

The study is a prospective, randomized, crossover trial (Figs. 2 and 3) of increased dry bean intake added to the participant’s usual diet (Intervention Diet), as compared to the participant’s usual diet excluding dry beans (Control Diet). Following an equilibration (control diet) period, sixty eligible subjects are randomized to one of two diet sequences - Control Diet then Intervention Diet *or* Intervention Diet then Control diet - with each subject acting as their own control. Canned beans are provided during the intervention period and multiple measurements are obtained at baseline and follow-up during each diet period in the sequence. Participants are free-living during the study period and able to choose and prepare their own meals, but are asked to not change any of their other usual habits for the duration of the study. To assess and monitor habitual behavior and adherence, participants are asked to complete web-based assessments at various time points during the study.

**Fig. 2 Fig2:**
[figure not shown]
CONSORT flow chart for BE GONE Trial

**Fig. 3 Fig3:**
[figure not shown]
Trial procedures and visit flow

### Recruitment and setting

Our main goals are to recruit a diverse set of high-risk CR patients with variation in basal diet and microbiome to address important research questions for future, multicenter trials; and a clinically well-characterized patient population that we can continue to follow over time. The study is conducted at The University of Texas MD Anderson Cancer Center main campus in Houston, Texas. Patients are actively recruited throughout MD Anderson with concentrated efforts in the colorectal screening, treating and survivorship clinics, as well as Kelsey-Seybold, a local referral clinic. Current and former patients are also identified via the institutional tumor registry and electronic medical records. Potentially eligible patients receive invitation emails or postcards with a brief but clear description of the study and procedures. Interested subjects are recruited either during a clinic visit or from inquiry via phone or email.

### Eligibility criteria

Recruitment is targeted to overweight or obese patients with a previous history of colorectal polyps or cancer. Full inclusion and exclusion criteria are included in Table 1.

**Table 1 Tab1:** BE GONE eligibility criteria

Inclusion Criteria	Exclusion Criteria
• Adult men and women at least 30 years of age • Meet criteria for overweight or obesity via body mass index (BMI) or waist size • Underwent colonoscopy screening within the past 10 years • History of pathology-confirmed precancerous polyp of the colon or rectum; OR colorectal cancer survivor who has completed treatment with adequate maintenance of bowel length (hemicolectomy or low anterior resection) and normalized bowel habits • English-speaking and reside in the greater Houston/outlying areas and/or willing to travel for study-related visits at MD Anderson • Ability to complete web-based dietary assessments twice per week • Willingness to provide stool samples and undergo venipuncture • Willingness to consume/avoid beans as instructed during the 16 weeks from randomization	• Antibiotic use in the past month and unable/unwilling to be deferred to a later recruitment date • Current smoker • Heavy drinker (defined as more than 14 drinks per week) • Currently taking exclusionary prescription medications (including cytokines, immunosuppressive agents, chemopreventive drugs, bile acid sequestrants/selective cholesterol absorption inhibitors) • Regularly taking anti-flatulence medications, probiotics and/or fiber supplements and unable/unwilling to discontinue for the purpose of the study • Major dietary restrictions relevant to the intervention • Total or near total colectomy, greater than 10 cm of small bowel resection • Hereditary colorectal cancer syndromes • Pregnant or lactating or planning to become pregnant

